### ***Withdrawal of Participants***

The investigator may withdraw a patient from the study treatment and follow-up procedures if the patient:

- Is in violation of the protocol;
- Experiences a serious or intolerable adverse event
- Develops, during the course of the study, symptoms or conditions listed in the exclusion criteria
- Requires early discontinuation for any reason

The investigator will also withdraw all participants from the study treatment if the study is terminated. Patients are free to withdraw from the study at any time upon their request or the request of their legally acceptable representative. Withdrawing from the study will not affect their access to standard treatment or their relationship with the hospital and affiliated health care professionals

When a participant is withdrawn from the treatment and/or the study by the investigator, the reasons for withdrawal shall be recorded and captured in the CRF by the site research assistant. Where the participant withdraws from the treatment and/or the study themselves or is withdrawn by their parent/guardian, the site research assistant shall attempt to ascertain the reason(s) for withdrawal from the parent/legal guardian or competent participant and, where provided, record this data. Any results obtained prior to withdrawal from the treatment and/or the study will be included in the analysis, unless the participant or their parent/guardian withdraws consent to use any of the participant's data.

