## 5.3 Consent

Consent will be sought from the parents of every child <2 years of age undergoing CPB for elective cardiac surgery over the study period. When the family is seen by the surgeons in pre-assessment clinic (usually days prior to surgery), the study will be mentioned to them by the surgeon. In addition, the study team will provide study information prior to hospitalization to families, including printed study flyers, and links to online study documentation (media release). A video detailing the study has also been prepared and is available to families. These will not replace consent, but support the consent process inasmuch as parents will have more time and more information available to

consider prior to consenting. Pre-admission contact can be made by phone, too, if not feasible directly. While parents may provide verbal consent, written consent will have to be obtained no later than the day of surgery in such circumstances.

The study team will meet the family and they will be given the study Information Statement and the consent form if they are interested. When the patient and family return to hospital for the operation, further explanation will be offered by a member of the research team and consent taken if the family wish to take part in the study. All endeavours will be made to consent parents by face-to-face meetings prior to the day of surgery, however due to the changing nature of that cardiac surgical bookings parents may be approached on the morning of surgery. Early phone contact with parents not present at the hospital or not attending pre-surgical clinics will be made. If parents give consent by phone it will be later confirmed by written consent during hospital/PICU stay.

The consent form will make it clear that standard medical treatment of children will be unaffected by participation in the study. Taking part is voluntary and will be free from coercion.

The research team will be available to field any questions from the parents prior to the consent form being signed.

The following basic principles of obtaining consent will be followed: Explain the project to the child's family in language that they understand. Generally, consent should be obtained in privacy and parents given as much time as possible to consider the study before consent.

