## **Sample size**

Pilot study data demonstrated a 66 hour (0.33 SD) reduction in VFDs associated with the study intervention [26]. Assuming a minimally clinically significant small effect size (0.2 SD), 90% power, two-sided alpha level of significance of 5%, 10% withdrawals, and 15% increase in sample size to account for a non-normal distribution of VFD, 1,320 patients are required (660 per group).

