## **Statistical analysis**

### *Statistical analysis principles*

- Analyses will be conducted based on the intention-to-treat principle. Specifically, patients who are eligible, who do not meet any exclusion criteria and who undergo randomisation will be analysed based on the treatment group they were allocated to, independent of the compliance with the treatment delivered.
- Participants who had more than one surgery before their second birthday will only have data related to their first surgery for which study consent was available analysed.
- Statistical tests will be two-sided applying a statistical significance level of 0.05. As we are not correcting for multiplicity when comparing secondary or other outcomes, such results will be considered exploratory and will be reported as point estimates with 95% confidence intervals (CIs).
- If there is missing data for the primary outcome measure for any participants, imputation methods will be used.
- Continuous variables will be assessed for normality; this will be undertaken using visual inspection of histograms and Q-Q plots.
- Standard descriptive statistics will be used when summarising variables; frequencies (percentages) for discrete variables, mean and standard deviation (SD) for continuous

variables, or, if continuous variables are non-normally distributed, median with interquartile range (IQR).

- This analysis plan and the primary manuscript will only include analyses up to 28 days. We will present analyses of postoperative delirium, health care costs, inflammatory markers and long-term outcomes (12 months and later post procedure) separately.
- Pre-planned subgroup analyses will be performed including the pre-defined study strata; these will be executed regardless of any potential treatment effect on the primary or secondary outcomes in the main cohort.
- To ensure transparency and reproducibility, the Stata code that will be used to analyse the final study data is available on GitHub (16).
- The trial statistician will be blinded to the treatment group until the analyses outlined in this SAP have been completed.
- Changes in the analysis plan by the investigators effective after publication of this SAP will be declared as such.

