## **Datasets analysed**

The Consolidated Standards of Reporting Trials (CONSORT) flow diagram will be presented based on all patients who were screened for the study. All other analyses will be performed on eligible patients who underwent randomisation, i.e. the intention-to-treat population independent of compliance with the protocol. If consent is not obtained or withdrawn, data will be excluded from the analyses, unless withdrawn patients permitted the use of data up to the point of withdrawal. The primary dataset for analysis will include baseline variables, surgical data, outcomes, adverse events and protocol deviations. Following completion of the data monitoring process, data and associated data transformation code will be extracted from the study REDCap database in a Stata (StataCorp Pty Ltd, College Station, Texas) format.

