#### *Treatment of missing data*

Missing data will be imputed for the primary outcome measure for any patients are missing one or more components required to calculate VFDs. Fully conditional specification will be used for imputation; the imputation model will include randomised treatment arm, study site and the two study strata variables. Ten sets of imputed data will be created using the methods described for the primary outcome. A pooled common effect estimate and 95% confidence interval will be generated from the imputed datasets.

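### Protocol 5.3 lets the investigator end follow-up for events that overlap the trial's own outcomes, and the SAP's imputation of ventilator-free days carries no information on severity

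*Combined protocol and SAP*

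**What the plan says.** Protocol 5.3, Withdrawal of Participants, opens its list of grounds with "The investigator may withdraw a patient from the study treatment and follow-up procedures". The grounds include a serious or intolerable adverse event and that the child "Develops, during the course of the study, symptoms or conditions listed in the exclusion criteria". On the data it says "Any results obtained prior to withdrawal from the treatment and/or the study will be included in the analysis", unless use of the data is refused. Nothing says that 28-day collection continues after the investigator withdraws a child.

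The exclusion list (5.1.2) includes ECLS, chronic ventilator dependency, an inotrope score of 15 or more, HFOV, cardiac arrest, septic shock, a need for inhaled or intravenous NO-pathway treatment, and methaemoglobin above 3%. Most items carry a preoperative time window. Several have a postoperative counterpart among the outcomes:

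- A score of 15 or more is one of the LCOS criteria (Protocol 7.2 Definitions; SAP S2).
- ECLS is part of the main secondary composite (SAP S2).
- Invasive ventilation and death make up VFD (SAP S2).
- Methaemoglobin above 3% is a named adverse event of NO (Protocol 8.1).

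Study gas ends when the child comes off bypass (Protocol 6.1).

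For missing VFD, the SAP (Treatment of missing data) says "the imputation model will include randomised treatment arm, study site and the two study strata variables". Imputation is planned for the primary outcome only, and SAP S2 counts missing LCOS items as no LCOS.

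On consent, SAP Datasets analysed says "If consent is not obtained or withdrawn, data will be excluded from the analyses, unless withdrawn patients permitted the use of data"; such permission covers only what was gathered before the child left. Protocol 6.2 says that intention to treat applies to incomplete data and to withdrawn consent.

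**The concern.** Once bypass is over, no study gas remains to be withdrawn unless the child has a later bypass operation. A clause that ends treatment and follow-up together then acts mainly on follow-up, and two of its grounds are more likely to be met by the children who do badly. If it is used, the missing 28-day data come from the bad tail of the VFD distribution.

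The planned imputation cannot see this. It assumes that, within arm, site and strata, a withdrawn child resembles a retained one. A child lost on day 3 on ECLS is imputed as an average child of that stratum. The SAP's sensitivity analysis adds covariates to the outcome models but does not relax this assumption. For LCOS, later time points missed after withdrawal count as event-free.

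If NO truly changes the number of children with a bad course, the two arms lose different numbers of such children, and the observed arms move closer together. A true benefit and a true harm are both understated. The 10% allowance for withdrawals in the sample size restores numbers, not representativeness.

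**Working it through.** **Planned sample size.** SAP Sample size gives 0.2 SD, 90% power, two-sided 5%, 10% withdrawals, 15% for non-normality, and a total of 1320. The base is 2 × (1.960 + 1.282)² / 0.2² = 526 per arm. Then 526 × 1.15 / 0.90 = 673 per arm (1346 in total), 526 × 1.15 × 1.10 = 666 (1332), and 526 × 1.25 = 658 (1316). All lie within 3% of 1320, so that figure is not in dispute. The implied SD is 66 h / 0.33 = 200 h, so 0.2 SD = 40 h.

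**Inputs for the bias.** Pilot LCOS in children under 2 years (Protocol Table 1) is p = 35.8% for control and 12.3% for NO, a gap of 0.235. Two assumptions are not in the documents: the VFD effect acts through LCOS status, and a share w of LCOS children is withdrawn before their VFD is known, equally in both arms.

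**Formula.** Imputing within arm gives withdrawn children the average of those retained. The apparent LCOS share is p′ = p(1 − w) / (1 − pw), and the fraction of the mean effect kept is (p′ control − p′ NO) / 0.235. The VFD cost of LCOS cancels.

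- w = 10%: p′ = 0.3222/0.9642 = 0.334 and 0.1107/0.9877 = 0.112. The fraction kept is 0.222/0.235 = 94.5%.
- w = 25%: p′ = 0.2685/0.9105 = 0.295 and 0.0923/0.9693 = 0.095. The fraction kept is 0.1997/0.235 = 85.0%.

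Power uses 660 × 0.90 / 1.15 = 516.5 effective children per arm and a standardised effect of 0.2 × the fraction kept.

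| w | Withdrawn, control v NO (of 660 each) | Overall | Mean effect kept | Power |
|---|---|---|---|---|
| 0 | 0 v 0 | 0% | 100% | 89.5% |
| 10% | 24 v 8 | 2.4% | 94.5% | 85.9% |
| 25% | 59 v 20 | 6.0% | 85.0% | 78.0% |
| 50% | 118 v 41 | 12.0% | 64.9% | 55.0% |

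At w = 25% the overall loss is still inside the 10% allowance, so it would not look unusual. On the 40 h design effect, losing 5.5% to 15.0% is 2.2 to 6.0 h.

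**Check by simulation.** There were 660 children per arm and 1000 runs. Assumed inputs were median ventilation of 5 days with LCOS and 1.2 days without (log-normal, log SD 0.9), and 28-day death of 10% and 1%. Imputation drew from retained children in the same arm.

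- With pilot LCOS rates and w = 25%, the mean difference falls from 1.69 to 1.43 days (85% kept) and the median difference from 0.59 to 0.44 days (74% kept).
- With LCOS of 25% in both arms and no effect, withdrawing 25% of LCOS children in each arm leaves Mann-Whitney rejection at 5.0% on the retained children.
- In the same null case, withdrawing 25% in one arm and 50% in the other raises rejection to about 26%.

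**The case against.** The strongest reply is that section 5.1.2 ties most items to the hours or days before surgery. Read strictly, postoperative ECLS or a high inotrope score is not on the list, and the clause has an ordinary use between randomisation and bypass. This stands in part. It makes the serious-adverse-event ground the firmer route, because that ground has no preoperative limit. But the exclusion-list ground is worded to run through the study, and section 5.3 does not say how preoperative windows apply afterwards.

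The plan also treats these events as expected outcomes (Protocol 8.1), verifies outcome items for every enrolled child (Protocol 7.6; SAP Data monitoring) and collects 28-day status with access to other hospitals' records (Protocol 7.2). That shows intent and feasibility, but no text says that collection continues after investigator withdrawal. The clause is permissive, and nothing shows that it has been used in this way. Results before withdrawal are kept, so an LCOS or ECLS event that triggers withdrawal is itself counted. The loss falls on 28-day VFD, death, length of stay and later LCOS time points.

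A reader might infer four stronger points that the documents do not support:

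- *Known deaths are imputed.* SAP S2 assigns zero to any child who dies within the window, so ventilated hours are not needed for that child. Only a death not ascertained after withdrawal would be missing.
- *The SAP deletes children withdrawn by the investigator.* Datasets analysed concerns consent. Investigator-withdrawn children stay in the set, without a complete outcome.
- *The ITT wording removes children who later meet an exclusion criterion.* The phrase "patients who are eligible, who do not meet any exclusion criteria and who undergo randomisation will be analysed" most naturally refers to eligibility at randomisation, though it gives no date.
- *Phone consent lets children be dropped once outcomes unfold.* SAP Randomisation requires informed consent first. Protocol 5.3 does sit uneasily with itself: it asks for written consent by the day of surgery after verbal consent, yet also says "If parents give consent by phone it will be later confirmed by written consent during hospital/PICU stay". The passages need reconciling, but no outcome-driven loss is shown.

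**Conclusion.** The gap in the plan is real and should be fixed, but it is not a fatal flaw. As written, Protocol 5.3 permits loss of follow-up that depends on the outcome, and no planned analysis addresses it.

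Under the stated assumptions, about 5–15% of the mean VFD effect would be lost if 10–25% of LCOS children were withdrawn. Three limits apply. The withdrawal share has no source in the documents. Using all LCOS children as the base is generous, since LCOS can also be met by lactate with oxygen extraction, which is not an exclusion criterion. The closed form concerns means, while the primary analysis is a Mann-Whitney test with a difference in medians. The simulation shows larger attenuation of the median, but on assumed distributions.

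It would be wrong to infer that the clause makes a false positive likely. Surgeons, anaesthetists and ICU staff are blinded (Protocol 6.1), and with equal withdrawal by arm the type I error holds. Withdrawal could become unequal through an arm-related ground such as raised methaemoglobin, but Protocol 6.1 reports similar values in both groups in earlier studies at the trial concentration. The expected consequence is attenuation.

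**What to change.** 1. **Protocol 5.3.** Separate stopping study treatment from stopping data collection. State that 28-day ventilation, vital status, LCOS, ECLS and length of stay are taken from hospital records for every randomised child unless parents refuse use of the data.
2. **SAP Treatment of missing data.** Add post-baseline severity (ventilated hours to last contact, LCOS, ECLS) and the RACHS score to the imputation model. Add a missing-not-at-random sensitivity analysis, such as a delta adjustment or VFD set to zero for withdrawn children.
3. **Consent and eligibility wording.** Reconcile the three rules on withdrawn consent: kept unless refused (Protocol 5.3), intention to treat (Protocol 6.2), and excluded unless permitted (SAP Datasets analysed). Reconcile the timing of written consent within Protocol 5.3. State in the SAP principles that eligibility is judged on facts from before randomisation.

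The cost is a short amendment and a few lines of SAP text. The data are largely routine records, and the protocol already provides for access to them. For children already enrolled, the outcomes could be abstracted retrospectively where consent allows. Reasons for withdrawal are already captured on the CRF, so a pooled, blinded count would replace the assumed withdrawal share before analysis. The sample size does not change. No view is taken on which clinical grounds for withdrawal are right.

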### ***General contact with families***

Prior to any contact being made with families, particularly following their PICU admission, all attempts will be made to determine the child's status via accessing hospital systems currently in place.

## **6 INTERVENTION**

## 6.1 Treatment arms

Patients allocated to the study gas arm will receive NO, which will be blended into the fresh gas flow kept at 3L/min for the CPB oxygenator with NO levels maintained at 20 ppm via an Ikaria INOmax DSIR (Ikaria, NJ, USA) or similar device. Continuous sampling of NO and NO2 concentration will be undertaken from an access port just prior to the oxygenator. NO will be started immediately when the patient is on CPB and ceased once coming off CPB at the completion of MUFing. Patients allocated to the Placebo arm will receive standard respiratory gases (oxygen-air mix) during bypass at a flow rate of 3L/min. Partial pressures of CO2 will be maintained constantly in both study arms as per the institutional practice.

*Note:* If patients require several CPB runs during the same procedure, the treatment has to be provided for each run using the same treatment allocation for every run (i.e. patients allocated to study gas arm will receive NO at 20ppm for every run).

**Subsequent CPB procedures:** Patients that were previously enrolled and randomised into the study with surgical procedure performed that required use of cardio-pulmonary bypass will not get re-randomised. Previously enrolled and randomised patients will undergo the same treatment allocation for subsequent surgeries, unless parents opt out. The study perfusionists at each study site have access to the treatment allocation, which will remain blinded for all other study team members.

**Blinding arrangements.** Of the investigating team, only the study perfusionist will be aware of the randomisation and NO delivery. Blinding arrangements in the operating theatre will be achieved by covering the NO delivery system with drapes. The dedicated study NO delivery system will be connected to the CPB oxygenator at all times, independent of randomisation. The surgeons, anaesthetists and ICU staff will be not aware which treatment arm a patient been allocated to. The perfusionists will be advised that all aspects of CPB except for provision of NO (or not) should be performed in a standard fashion for study participants. The perfusionist does not attend the surgical handover in PICU. The Data Safety Monitoring Board will be unblinded in the event of a severe adverse event. In our pilot study and the previous published study by Checcia, methaemoglobin values using NO at 20 ppm were similar in both the control and intervention groups (1.4%) [29].

**Perioperative Care.** Techniques of anaesthesia, surgical technique or method of CPB perfusion will not be specified apart from some details of perfusion. *Rationale:* To allow site specific individual practice and not to interfere with centre specific cardiac surgical load and outcome.

All patients will receive a minimum sweep gas flow of 3.0 l/min and CO2 will be added to maintain PaCO2 35–40 mmHg to ensure NO mixing and delivery in the intervention group. Sweep gas will be set as per standard CPB practice.

**Note:** Patients undergoing CPB that are considered by treating physicians (surgeons, anaesthetists, or intensivists) to require inhaled NO can receive iNO at any time during or after CPB, independent of treatment allocation, delivered as an inhalational gases at the doses defined by the clinicians (usually 0 to 20ppm).

**Postoperative Care.** The postoperative care will be performed as per site specific standard protocol/care for all patients without any specific definition of any procedures or interventions.

Inotrope delivery, fluid management, renal replacement therapy, iNO, or indication for ECLS will be provided as per standard care locally. *Rationale:* Site specific intensive care practice shall continue for the trial.

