#### 5.1.2 Exclusion criteria

- Signs of persistently elevated pulmonary vascular resistance preoperatively requiring iNO or preoperative intravenous use of drugs involved in the NO pathway such as GTN, within 48 hours prior to CPB (oral sildenafil treatment alone is not an exclusion).
- Patient is on ECLS immediately prior to surgery

- Chronic ventilator dependency
- Concurrent known confirmed bacterial sepsis/septic shock, diagnosed within <48 hours prior to surgery and being actively treated with antibiotics at time of surgery (suspected sepsis treated with antibiotics is not an exclusion criteria unless inotropes are required for treatment of septic shock at time of surgery)
- Preoperative acute respiratory distress syndrome requiring HFOV ventilation <48 hours of surgery
- Patient requires high doses of vasoactive drugs prior to surgery with an inotrope score  $\geq 15$  met within 24 hours prior to surgery: Inotrope requirement will be calculated by means of the Vasoactive-Inotrope Score (VIS) (2):  $VIS = \text{dopamine dose (mcg/kg/min)} + \text{dobutamine dose (mcg/kg/min)} + 100 \times \text{adrenaline dose (mcg/kg/min)} + 100 \times \text{noradrenaline dose (mcg/kg/min)} + 10 \times \text{milrinone dose (mcg/kg/min)} + 10,000 \times \text{vasopressin dose (U/kg/min)}$ .
- Cardiac arrest within one week (7d) prior to surgery
- Emergency cardiac surgery which may preclude obtaining informed consent (defined as acutely required life-saving procedure in a patient unlikely to survive the next hours without the surgery)
- Pre-existing methaemoglobinemia (MetHb > 3%)

NB. Patients that were previously enrolled and randomised into the study with surgical procedure performed that required use of cardio-pulmonary bypass will not get re-randomised. Previously enrolled and randomised patients will undergo the same treatment allocation for subsequent surgeries, unless parents opt out. Rationale: For patients undergoing same procedures, any potentially additive protective impact of NO during CPB on long-term neurodevelopment may become diluted by use of CPB without NO during subsequent procedures. We expect that ca. 10% of all CPB cases <2 years may require subsequent CPB <2 years of age.

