## 8 ADVERSE EVENTS AND RISKS

### 8.1 Definitions

Adverse Event (AE) is any untoward medical occurrence in a patient enrolled into this study regardless of its causal relationship to study treatment intraoperatively and ***within the first 48 hours postoperatively.***

Serious Adverse Event (SAE) is any AE that results in:

- Death
- Is life-threatening
- Requires prolongation of existing hospitalisation
- Results in persistent or significant disability/incapacity
- Requires intervention to prevent permanent impairment or damage

**Specific AEs related to NO delivery during CBP: air embolism, severe hypotension during bypass and increased MethHb (MethHb is >3%).** For the purposes of this study the site investigator is responsible for recording all AEs, regardless of their relationship to study intervention, for the period from randomisation until completion of each individual child's participation in the study.

This study is performed in infants and children undergoing high risk cardiac surgical procedures with death or high risk organ support such as ECLS or renal replacement therapy within the expected outcome. We will report all SAE including deaths and the investigators will give clinical recommendations if the death was unexpected and reason for further investigation by the DSMB.

Additional screening for adverse events will occur at the time of patient discharge from hospital.

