| Blood products received in theatre                     |                    |                     |                     |
| Red blood cells (mL/kg) median (IQR)                   |                    |                     |                     |
| Whole blood (mL/kg) median (IQR)                       |                    |                     |                     |
| Platelets (mL/kg) median (IQR)                         |                    |                     |                     |
| Fresh frozen plasma (mL/kg) median (IQR)               |                    |                     |                     |
| Cryoprecipitate (mL/kg) median (IQR)                   |                    |                     |                     |
| Drug treatments received in theatre                    |                    |                     |                     |
| Intravenous steroids n (%)                             |                    |                     |                     |

|                                                                                                          |  |  |  |
|----------------------------------------------------------------------------------------------------------|--|--|--|
| Inhaled NO n (%)                                                                                  |  |  |  |
| Administration of study drug (nitric oxide)                                                       |  |  |  |
| Time from start of CPB to start of NO (min) mean (SD)/median (IQR)                                |  |  |  |
| Duration of NO on CPB (min) median (IQR)                                                          |  |  |  |
| Proportion of time spent on CPB with NO* mean (SD)/median (IQR)                                   |  |  |  |
| Change in methaemoglobin level (%) between start and post-CPB mean (SD)/median (IQR) ^ |  |  |  |
| Change in methaemoglobin level (%) between start and post-CPB >3% ^ n (%)              |  |  |  |

390     \* if multiple CPB runs during the same surgery, summarising every CPB run individually; ^ calculated as post-CPB methaemoglobin – pre-CPB

391     methaemoglobin

392     IQR interquartile range; CPB cardiopulmonary bypass; SD standard deviation; NO nitric oxide

393 Table 3. Primary and secondary outcomes per intention-to-treat analysis

394

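### The protocol names a methaemoglobin level above 3% as a harm of NO delivery, but the SAP's only threshold row counts a change above 3%, for the NO arm only

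*Combined protocol and SAP*

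**What the plan says.** **The intervention.** Protocol section 6.1 gives the NO arm nitric oxide, "which will be blended into the fresh gas flow kept at 3L/min for the CPB oxygenator with NO levels maintained at 20 ppm".

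**The harm.** Protocol section 8.1 lists three adverse events specific to NO delivery during bypass: air embolism, "severe hypotension during bypass and increased MethHb (MethHb is >3" per cent). The MetHb criterion is an absolute level. Section 5.1.2 excludes children on the same level: "Pre-existing methaemoglobinemia (MetHb > 3" per cent).

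**The data.** Section 7.2 puts MetHb on the list of surgical and bypass data, and again on the postoperative list, with no restriction by arm.

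**The SAP tables.** Table 2 has two MetHb rows, both under the block on administration of the study drug. One summarises the change as a continuous variable. The other is a count: "Change in methaemoglobin level (%) between start and post-CPB >3" per cent. The footnote defines the change as the post-CPB value minus the pre-CPB value, so the threshold is 3 percentage points. The SAP section *Surgical procedure and intervention characteristics* says that compliance with the study drug is reported only for patients randomised to the intervention. Table 3 has no MetHb row.

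**The SAP safety text.** *Safety outcomes* sends reactions judged possibly, probably or definitely related to the supplement. It compares the arms on one quantity, the proportion with at least one adverse event. The planned supplement includes a listing of adverse events.

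**The concern.** The protocol and the SAP put the same number, 3%, on two different quantities. The protocol uses the level reached, for any child. The Table 2 row uses the rise from baseline, for NO children only. A reader who looks in the SAP tables for the protocol's named harm will find a stricter count with no control-arm comparator.

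MetHb is one of only three harms that the protocol ties specifically to the intervention, and it is measured objectively. The protocol itself supports the safety of 20 ppm with a between-group statement: in section 6.1, under the blinding arrangements, it reports earlier values as similar in control and intervention groups (1.4%). A trial of 1,320 children could give a far more precise version of that comparison, but the plan does not specify one. The pooled comparison of any adverse event mixes MetHb with everything else that can follow bypass surgery in this population, so it cannot stand in for one.

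**Working it through.** The documents give no MetHb event rate and no planned MetHb analysis, so there is no plan figure on this point to reproduce. The check compares the two rules and then illustrates the effect of pooling.

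**1. The two rules.**
- Protocol adverse event, applied to the post-CPB value: post > 3.
- Table 2 row: post − pre > 3, that is, post > pre + 3.

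Because pre is never negative, every child in the Table 2 row also exceeds 3%. The reverse fails for any pre-CPB level above zero: a child with 3 < post ≤ pre + 3 meets the protocol level and is not in the row.

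**2. Size of the missed band.** The pre-CPB level is an assumption. The only MetHb value in the documents is 1.4% (section 6.1), which is not described as a pre-CPB value. Section 5.1.2 caps the eligible baseline at 3%.

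| Assumed pre-CPB level | Table 2 row starts above | Levels missed |
|---|---|---|
| 0.5% | 3.5% | over 3% to 3.5% |
| 1.0% | 4.0% | over 3% to 4.0% |
| 1.4% | 4.4% | over 3% to 4.4% |
| 2.0% | 5.0% | over 3% to 5.0% |
| 3.0% | 6.0% | over 3% to 6.0% |

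Example: 1.4% before and 3.5% after gives a change of 3.5 − 1.4 = 2.1. The level exceeds 3 and the change does not.

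**3. Why the pooled comparison does not replace a MetHb row.** Let m be the MetHb rate in an arm and q the rate of any other adverse event, equal in both arms and independent of MetHb. Then P(any event) = 1 − (1 − q)(1 − m), and the difference between arms is (1 − q)(m_NO − m_control). Pooling shrinks the excess by the factor 1 − q and adds the variance of the other events.

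Illustration with the planned 660 per group. All rates are assumed: m = 2.5% (NO) and 0.5% (control), with q from 10% to 50%.
- MetHb row: difference 0.025 − 0.005 = 0.020; SE = √(0.025×0.975/660 + 0.005×0.995/660) = 0.00667; 95% CI 0.7 to 3.3 points.
- Any event, q = 10%: 12.25% v 10.45%, difference 1.8 points (−1.6 to 5.2).
- Any event, q = 30%: 31.75% v 30.35%, difference 1.4 points (−3.6 to 6.4).
- Any event, q = 50%: 51.25% v 50.25%, difference 1.0 point (−4.4 to 6.4).

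The SAP would report the any-event comparison by logistic regression. Risk differences are used here only to put the two on one scale.

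**4. If there are no events.** A by-arm row is informative even then. With 0 of 660 in one arm, the exact 97.5% upper bound is 1 − 0.025^(1/660) = 0.56%.

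**The case against.** The best defence is that the Table 2 row was never meant to measure harm. It sits among compliance descriptors, and a compliance measure need not use the adverse-event threshold. That is correct. A reader might infer that the SAP redefines the adverse event or lets it disappear, and the documents do not support that: the level above 3% stays a named event in section 8.1, is recorded whatever its relationship to treatment, enters the any-event comparison and appears in the listing.

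Three further points carry weight:
- A reader might infer that the report will hold no by-arm information on MetHb. That is too strong. The listing may be split by arm, and the SAP does not say either way. What can be said is that no MetHb-specific estimate is pre-specified.
- The restriction to the NO arm comes from the SAP text together with the block heading. Table 2 itself has columns for standard care and for the difference. The reading is clear, but the table alone does not state it.
- The rates in step 3 have no source. The one MetHb figure in the documents, 1.4% and similar in both groups, gives no support for a five-fold excess, and any pooled endpoint dilutes its components. The illustration shows only how a signal would be hidden if there were one.

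A reader might also infer a conflict in the dosing instructions, because section 6.1 has the flow fixed in the NO arm and, in the control arm, "during bypass at a flow rate of 3L/min", while *Perioperative Care* says "All patients will receive a minimum sweep gas flow of 3.0 l/min" and "Sweep gas will be set as per standard CPB practice". The documents do not support treating this as a finding. The later text gives the working rule, a minimum for all patients, and its purpose of ensuring NO mixing and delivery. NO is held at 20 ppm under either wording, and continuous sampling of its "concentration will be undertaken from an access port just prior to the oxygenator". No effect on any result is shown. It is a drafting matter.

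**Conclusion.** The point holds as a minor reporting gap. The protocol's named harm is an absolute level. The SAP's only threshold row uses a change, is stricter for every child with a baseline above zero, and is confined to the NO arm. At an assumed baseline of 1.4% it misses levels from just over 3% up to 4.4%; across assumed baselines of 0.5% to 3% the upper end of the missed band runs from 3.5% to 6%. How many children fall in that band cannot be known from the documents.

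That the two rules differ, and that no MetHb-specific between-arm estimate is specified, follows from the text alone. The size of the band rests on the assumed baseline, and the dilution figures rest on assumed rates and independence. The primary analysis, alpha, power and sample size are unaffected.

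**What to change.** Add one row to the SAP tables, in place of or beside the change > 3% count: number and percentage of children with post-CPB MetHb above 3%, in both arms, with the difference and 95% CI. Give the number with a post-CPB value in each arm as the denominator. If counts are small, use an exact or score interval. Keep the continuous change row, for the NO arm, as the compliance descriptor.

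**Cost.** One table row. MetHb is on the collection list in section 7.2 without restriction by arm, so no new measurement should be needed, provided that post-CPB values were entered for control children as well. Because the SAP commits to declaring later changes to the analysis plan, the row can be added and labelled as such.

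**Downside.** A level threshold also counts children who were already near 3% before bypass. Showing both arms side by side and keeping the change row makes these visible.
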